## **10. Trial medication**

### **10.1 General information**

The TRK inhibitor, CT327, is a topical investigational medicinal product (IMP) currently being developed by Creabilis Limited for the treatment of pruritus and pain in dermatological conditions. This trial is the first trial to investigate the use of CT327 in patients with CYLD defective skin tumours, however the drug has been given to 36 healthy volunteers and 185 patients in previous clinical trials. Safety data can be found in the CT327 Investigator Brochure. Creabilis Ltd will supply study ointment (active and placebo) to the NuTH research pharmacy team for use exclusively in this trial. For reported side effects of CT327 please refer to Section 18 Pharmacovigilance.

Please refer to the Investigator Brochure for more detail.

### **10.2 Medication Blinding**

#### **10.3 Cohort 1**

Cohort 1 is open label. Patheon UK Ltd ([name]) will be responsible for manufacture and packaging of the CT327 ointment. AndersonBrecon trading as Packaging Coordinators Inc (PCI) will be responsible for the labelling of the CT327 ointment and for sending a sufficient supply to NUTH pharmacy. The CI, or delegate, will notify the pharmacy when each patient is recruited to cohort 1 and complete the necessary prescription requests. NUTH pharmacy will then dispense the drug as required by the protocol.

#### **10.4 Cohort 2**

Cohort 2 is randomised and double blinded. Patheon UK Ltd will be responsible for manufacture and packaging of the CT327 and placebo ointment. AndersonBrecon trading as PCI will be responsible for the labelling of the supplies of CT327 and placebo ointment against the master randomisation list provided to them by the trial statistician. AndersonBrecon trading as PCI will supply sufficient CT327 and placebo ointment to NUTH pharmacy. The Chief Investigator and trial management team will be notified each time a patient is randomised by an automated email from the randomisation service backed up by notification via the research team (this is likely to be the person doing the randomisation, research nurse or trial manager depending on local arrangements). This information will enable the CI, or sub-investigator, to make the necessary prescription requests as per the randomisation allocation. NUTH pharmacy will then dispense the CT327 and placebo ointment to each patient as required.

The code for tumour treatment assignment will be kept locally by a third party who will not be responsible for patient care (in the hospital pharmacy). In the event of an emergency should the treatment assignment be needed, the clinical trials pharmacist at the Royal Victoria Infirmary (during normal working hours) or the on-call pharmacist (outside normal working hours) can be contacted to break the blinding (preferably with authorisation from the Chief Investigator) and the Chief Investigator immediately informed.

When the blinding code is broken the reason will be documented in the trial case report form (CRF) and in the patient's notes. See section 13 'Trial Blinding' for further information.

## 10.5 Drug Supplies

The study treatments are 0.5% w/w CT327 ointment or vehicle (placebo) for topical administration. The ointment contains butylated hydroxytoluene (BHT), benzyl alcohol, propylene glycol, white soft paraffin, white beeswax, stearyl alcohol and cholesterol. In addition the active ointment contains CT327. CT327 ointment and matching placebo ointment (vehicle) will be manufactured by Patheon UK Ltd ([name]). Patheon UK Ltd will package the CT327 ointment and matching placebo ointment (vehicle) in 20g amber glass jars. Labelling for ointments (for cohort 1 and cohort 2) will be performed by AndersonBrecon trading as PCI. The test materials will be identified by the lot, batch numbers, expiry date and certificate of analysis. CT327 ointment and vehicle will be supplied to NUTH pharmacy by AndersonBrecon trading as PCI and will arrive packaged and labelled as per the requirements of cohort 1 (unblinded CT327 ointment only) and cohort 2 (blinded CT327 ointment and vehicle according to the master randomisation list supplied by the trial statistician).

## 10.6 Treatment Packaging and Labelling

Patheon UK Ltd ([name]) will be responsible for treatment packaging. AndersonBrecon trading as PCI ([name]) will be responsible for treatment labelling. These products will be released to NuTH. AndersonBrecon trading as PCI will be responsible for labelling the active ointment for cohort 1 (open label) and will be responsible for the labelling of the individual CT327 or vehicle ointment jars, with appropriate labels (cohort 1: CT327 0.5% w/w, cohort 2: CT327 0.5% w/w or placebo) according to the randomisation schedule for the trial.

## 10.7 Drug Storage Conditions

Study medication should be stored at ambient room temperature (15-25°C), in a controlled access area.

The ointments have a shelf life of 24 months at ambient temperature on the basis of ongoing 3 year ICH stability studies (as stated in investigators brochure).

## 10.8 Drug Accountability

AndersonBrecon trading as PCI will be responsible for certification of the finished IMP and will perform QP release. Study medication will be maintained under adequate security by appropriate site personnel (e.g. pharmacist) and in accordance with applicable regulatory requirements. Trial medication (including vehicle) remaining at the end of the trial will be returned to AndersonBrecon trading as PCI who can destroy and send destruction records to Creabilis.

Trial medication will be prescribed by a trial clinician, and dispensed to the patient or clinical staff according to local pharmacy policy. Patients in possession of their trial medication shall return all trial supplies in their original packaging (even if empty) to the research team who will pass it to the pharmacist at 4 weeks for cohort 1 and at 4 and 12 weeks for cohort 2. All returned, or unused, trial medication will be stored in pharmacy until the end of the trial, or until the trial manager has completed appropriate reconciliation in collaboration with pharmacy staff.

Documentation of prescribing, dispensing and return of trial medication shall be maintained for trial records.

Patient compliance with treatment will be monitored by means of patient diaries which will be reviewed by the trial team.

The investigator or designee must maintain adequate records of receipt and distribution of all trial medication, using appropriate accountability records.

## **10.9 Drug Administration**

At the first trial visit, patients will have their tumours for drug administration identified; details for each cohort are stated in the inclusion/exclusion criteria (section 9). They will then be instructed on how to administer the trial medication and given patient instructions to take away for reference.

A new disposable finger stocking should be used for each separate administration and disposed of after use. The amount of drug will be measured using a provided spatula. The patient will also be instructed to wash the area with warm water before administration. The full tumour should be covered being careful to not administer treatment to any surrounding areas. The ointment should be spread evenly over the area. The ointment should be applied in the evening, 2 hours before bedtime.

### **11.7.1 Cohort 1**

In cohort 1 active trial medication containing CT327 at 0.5%w/w will be provided as ointment in 20g glass jars. Patients will be provided with a spatula to help them to apply the correct amount of ointment.

The dose will be one application (2 standardised spatulas) in the evening to each tumour as directed at the first visit by the research nurse/doctor. Application will be recorded in a patient diary.

In cohort 1 participant's will treat their selected tumour with the active treatment for a 4 week period.

A telephone contact number will also be provided so participants can contact a member of the research team if required.

Any participant reporting significant side effects will be reviewed in clinic.

### **11.7.2 Cohort 2**

In cohort 2 active and placebo trial medication will be provided at baseline and visit 4 to supply enough ointment for the 12 week period. Active medication will contain CT327 at 0.5%w/w. Each participant pack of active medication or placebo will be presented as a 20g glass jar.

The dose will be one application (1 standardised spatula) in the evening to each tumour as directed at the first visit by the research nurse/doctor. Patients will record application of treatment in a patient diary (Appendix C).

In cohort 2 all participants will be treating tumours on one half of the body with active CT327 and the other half of the body with placebo according to the randomisation allocation for a 12 week period. A telephone contact number will be provided so participants can contact a member of the research team if required.

Any participant reporting significant side effects will be reviewed in clinic.

A two day visit window is allowed for the second dispensing visit at week 4.

### **10.10 Concomitant Medication**

For management of concomitant therapies, please refer to the Investigator Brochure. A complete listing of all concomitant medication received during the treatment phase must be recorded in the relevant CRF.

## **11. Randomisation (cohort 2 only)**

A member of the trial team (as outlined in the delegation log) will re-check and confirm eligibility prior to randomisation. Eligibility can be confirmed by using information obtained from patient's notes and directly from the trial participants.

Randomisation will be at the per patient level randomising active and placebo treatments to left or right sided application. There will be no stratification at randomisation in this small early phase trial.

The statistics team will be responsible for preparing the allocation lists which will be uploaded to a secure web-based system by the database manager.

Randomisation will be administered centrally by the Newcastle Clinical Trials Unit internet-accessed secure web-based system which provides ease of operation, with in-built validation/plausibility checks at time of data entry.

The PI at site or an individual with delegate authority will access the web based randomisation system. Patient screening ID and initials will be entered into the web-based system. Patients will be allocated both active and placebo treatments to be applied randomly to left or right tumours (e.g. Group1: L=active; R=placebo, Group 2: L=placebo; R=active, where the terms L and R refer to the patient's left and right side). Patients allocated to a specific group (e.g. Group1: L=active; R=placebo), will remain in this same group when prescriptions are dispensed at baseline and week 4. Specific training will be given at site initiation.

**The randomisation service website is accessed at: <http://apps.ncl.ac.uk/random/>**

**Queries about the randomisation system can also be addressed to:**

**[[contact]](mailto:[contact])**

Practicalities of the randomisation of tumours to each arm of the trial:

4 or 5 tumours matched for size will be selected on each side of the patient. Each tumour will be assigned a number to facilitate assessments and then each side of the patient will be allocated randomly to receive either active ointment or placebo ointment.

Photographs will be taken and the tumours numbered clearly so that the patient can refer to the tumour maps to ensure the correct tumour is being treated from the correct ointment jar.

Tumours will be marked with a 2mm dot using a permanent marker designed for use on the skin, which the patient will renew as necessary. Tumours within the hair will have a small amount of surrounding hair trimmed to allow the patient to locate the tumour by feel, and for volume assessments.

## **12. Trial Blinding (Cohort 2 only)**

Patients and investigators will be blinded to the treatment allocation. Those responsible for tumour volume measurements, histology assessments and molecular analysis will also be blinded to treatment allocation. The Trials Management Group including Trial Manager will be blind to the treatment allocation. The trial statistician may provide confidential unblinded data to the closed session of the external independent data monitoring committee (excluding members of the Trials Management Group).

Following the unlikely event of a code break, patients' will continue to be followed up if they agree to do so. If the unblinding reveals that the cause was the placebo ointment, patients will be offered the continuation of the trial medication as per the randomisation if they wish. The analysis of the trial will reflect the unblinding, data both including and excluding the unblinded participants will be analysed to avoid bias.

Code breaks will not be routinely performed for all participants who complete trial treatment but all patients may be informed of their allocations once the trial analysis is complete on request and the data released to the chief investigator.

At the final visit, the integrity of the blind will be assessed by asking the participants: Which side was receiving active treatment? Why do you think this?" on the patient treatment questionnaire. The treatment assessor will be asked to record their answer on a separate CRF and prior to asking the participant to avoid bias.

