#### **8.4 Cohort 2 Exclusion criteria:**

- Patients aged <18 years
- Patients without multiple CYLD defective tumours
- Pregnancy or lactation
- Women of childbearing age and sexually active men whom do not wish to use contraception whilst on the study
- CYLD defective tumours which are ulcerated or have recently changed (these tumours will be managed according to standard practice of care)
- Severe incapacity of higher function such that fully informed consent cannot be achieved, to be determined by clinical judgement
- Significant concurrent illness
- Patients who developed an adverse reaction to CT327 in cohort 1 (score of 4 or above on the modified Draize score)
- Patients who have taken part in cohort 1 and not completed a minimum 2 week treatment free washout period
- Large tumours >2cm base diameter will not be eligible
- Any tumour within 10cm of an excision scar of a cohort 1 treated site will not be eligible
- Use of any other topically administered treatments at the treatment site

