### **15.2 Withdrawal of participants**

Trial drug must be discontinued if:

- The participant decides they no longer wish to continue
- Cessation of trial drug is recommended by the investigator
- Pregnancy
- Any significant medical condition (in the judgement of the site investigator)
- Localised reactions:

Any patient reporting treatment site reactions will be assessed in the clinic. A modified Draize score of 4 or above would result in discontinuation of the drug. In the event of such an adverse reaction, blinding may need to be broken to determine if the reaction is related to the application of the trial drug to the treated site. Once the blind is broken, the trial drug will need to be discontinued if it is found to be responsible for the adverse event.

- Systemic reactions:

Any other reported side effects/adverse events that the patient experiences during the trial will be assessed by the chief investigator. If clinically appropriate, the patient will be reviewed in clinic and a decision made regarding discontinuing the trial drug if it is feasible that this is related to the trial drug.

Participants have the right to completely withdraw from the trial at any time for any reason, and without giving a reason. The investigator also has the right to withdraw patients from the trial drug in the event of inter-current illness, adverse events, serious adverse events, suspected unexpected serious adverse reactions, protocol violations, cure, administrative reasons or other reasons. It is understood by all concerned that an excessive rate of withdrawals can render the trial uninterpretable; therefore, unnecessary withdrawal of patients should be avoided. Should a patient decide to withdraw from the trial, all efforts will be made to report the reason for withdrawal as thoroughly as possible. Should a patient withdraw from trial drug only, efforts will be made to continue to obtain follow-up data, with the permission of the patient.

Participants who wish to withdraw from trial medication will be asked to confirm whether they are still willing to provide the following.

- 'end of trial data' as per visit 3 (4 weeks) in cohort 1 or visit 4 (12 weeks) in cohort 2, at the point of withdrawal

- If participants agree to the above, they will be asked to complete a confirmation of withdrawal form to document their decision.

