## **6. TREATMENT RECEIVED**

Phase 1b will be open label and Phase 2a will be a randomised double blind trial.

In both Phases the dose will be one application in the evening to each tumour as directed at the first visit by the research nurse/doctor. Application will be recorded in a patient diary.

In Phase 1b the participant's will treat their selected tumour with the active treatment for a 4 week period. In Phase 2a all participants will be treating tumours on one half of the body with active CT327 and the other half of the body with placebo according to the randomisation allocation for a 12 week period.

Withdrawals from treatment are cases where the trial drug is discontinued. This may be because the participant decides they no longer wish to continue, cessation of the trial drug is

recommended by the investigator, the participant is pregnant, there is a significant medical condition or an adverse localised or systemic reaction. In both cohorts, participants who withdraw from trial drug prior to the end of treatment visit, will be followed up and included in the analysis, if they are happy to do so.

The analysis sets are the Phase 1b treatment set and the Phase 2a treatment set.

Compliance to the treatment will be reported (Appendix 2) at the patient level as the percentage compliance in terms of days of missed ointment for all tumours. If additionally individual tumours have had missed treatment this will be reported at the tumour level as the number of missed applications (in days) as reported in the diary cards. The total number of applications, at the tumour-level, will be also be reported as median days (IQR, range), over 4 weeks in Phase 1b and over 12 weeks in Phase 2a.

The expected number of applications in a 4-week (28 day) period is 28 and in a 12 week (84 day) period is 84 (+/-3 days dependent on EoT visit date). Compliance to treatment will be summarised as the number of days on treatment (date end-date start) as recorded in the patient diary and reported as median (IQR, Range), as well as the proportion of protocol treatment received, calculated as the number of days of applications as a proportion of the 28/84 day protocol treatment, and reported with 95% Confidence Interval (CI).

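### After a severe site reaction in cohort 2, lasting discontinuation can turn on a code break, and neither a restart step nor the extent of the stop is stated

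*Combined protocol and SAP*

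**What the plan says.** Protocol section 15.2 lists the situations in which trial drug has to stop. Under localised reactions it says: "A modified Draize score of 4 or above would result in discontinuation of the drug". That sentence carries no condition on allocation and mentions no pause or restart. The same bullet then allows the blind to be broken to judge relatedness, and continues: "Once the blind is broken, the trial drug will need to be discontinued if it is found to be responsible for the adverse event".

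Protocol section 12 covers what follows a code break in cohort 2: "If the unblinding reveals that the cause was the placebo ointment, patients will be offered the continuation of the trial medication". Continuation is on the allocated sides and at the patient's choice.

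Section 10.5 describes the placebo as the vehicle, lists the ingredients of the ointment, and adds: "In addition the active ointment contains CT327". Each cohort 2 patient uses both ointments, one on each side of the body (section 11, and the cohort 2 part of section 10.9, numbered 11.7.2).

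On the extent of a stop, section 15.2 speaks of participants who withdraw from trial drug. SAP section 6 does the same; its reasons for withdrawal include that "there is a significant medical condition or an adverse localised or systemic reaction". Neither says whether one jar or both are stopped.

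**The concern.** A score of 4 is severe inflammation, and a score of 5 adds oozing, crusting or ulceration (Appendix A). The clinic needs one clear instruction for that event. As written, the first sentence of the bullet stops treatment outright, while the later sentence and section 12 let the lasting decision depend on which ointment the code break reveals.

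Three things are at stake. The first is safety, because the case in which continuation is offered is the one that points to an ingredient base found in both jars. The second is the blind, which is opened for a decision that does not need it. The third is who stays in the Phase 2a protocol set, which requires 12 completed weeks of treatment (SAP section 5.1).

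**Working it through.** The plan gives no figure for this point, so the check is of the text, with a short tumour count at the end.

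**Step 1: follow one event through the rules.** Take a score of 4 or 5 on one side of a cohort 2 patient.

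| Reacting side | Code broken? | 15.2, score sentence | 15.2, later sentence | Section 12 |
|---|---|---|---|---|
| Either | No | Stop | Not engaged | Not engaged |
| Active | Yes | Stop | Stop if the drug is held responsible | No offer |
| Placebo | Yes | Stop | No stop required, if trial drug here means CT327 | Continuation offered |

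The same placebo-side reaction ends treatment if nobody breaks the code, and leads to an offer to continue if somebody does. Section 12 does not mention the Draize score. The link is that 15.2 allows a code break for this event and section 12 sets what follows a code break.

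**Step 2: try to reconcile the texts.** They fit together as stop, unblind, resume if placebo was the cause. For that to be the rule, the first stop must be temporary, and no section says so. On this reading the lasting decision still depends on the revealed allocation.

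**Step 3: ask what the code break adds.**
- Which jar is involved: already known, because each side has its own ointment.
- Whether the ointment on that side should stop: the score answers this.
- Whether the other side is at risk: if the placebo ointment was the cause, the cause is the vehicle, and by section 10.5 the active jar contains that vehicle too. Continuing as allocated means continued vehicle on both sides.

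**Step 4: ask what the code break discloses.** Left and right are complementary, so one break gives the allocation of every tumour in that patient: 4 + 4 = 8 or 5 + 5 = 10. The Chief Investigator is informed at once (section 10.4). Because section 12 makes the offer only when placebo was the cause, the offer itself tells the patient which side was placebo.

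**Step 5: size in the analysis sets.** Inputs: 4 or 5 tumours per side (protocol sections 7.2 and 11; SAP section 3.2) and 75 tumours per arm (protocol section 14.2).
- Share of one arm contributed by one patient: 4/75 = 5.3%; 5/75 = 6.7%.
- Placebo-side reaction, both jars stopped for good: each arm of the protocol set falls to 75 - 4 = 71 or 75 - 5 = 70.
- Same reaction, section 12 followed and the offer accepted: treatment of the same 8 to 10 tumours can continue, and they can remain in the protocol set.

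The protocol-set figures assume that all 75 tumours per arm would otherwise qualify. The documents give no rate for scores of 4 or above, for placebo-side reactions or for code breaks, so no expected number of affected patients can be stated.

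**The case against.** The strongest reply is that nothing conflicts. The 15.2 bullet runs in clinical order (assess, stop, unblind if needed, keep stopped if the drug is responsible) and section 12 supplies the other branch. In the code-break sentences, trial drug most naturally means CT327, since otherwise unblinding could not settle relatedness. Sections 12 and 15.2 then agree that continuation may depend on allocation, which makes it a deliberate choice. This much stands: a reader might infer two irreconcilable rules, and the documents do not support that. What remains is an unstated restart step and a choice that is weak on its merits because of the shared vehicle.

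The safeguards also count. Reactions are assessed in clinic, the patient may decline to continue, and the drug must stop where "Cessation of trial drug is recommended by the investigator". An investigator can therefore prevent re-exposure. But the plan does not tell the investigator that the shared vehicle is a reason to do so, and the default it sets is an offer to continue.

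On extent, the per-participant wording hints at both jars stopping, and the left and right diary rows, the tumour-level compliance reporting and the patient-or-tumour analysis sets could handle either. That shows the data can cope; it does not tell the clinic what to do.

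A reader might also point to section 8.4, which bars from cohort 2 anyone who scored 4 or above in cohort 1, as proof that the plan is stricter elsewhere whichever component was to blame. That goes too far. It is an entry criterion worded as a reaction to CT327. That it also catches vehicle reactions is only an inference from cohort 1 having used active ointment alone.

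**Conclusion.** The point holds as an unclear and poorly chosen stop rule. Lasting discontinuation after a severe reaction can depend on a code break that the decision does not need, the restart is not described, the extent of the stop is not stated, and a patient with a severe vehicle reaction may be offered continued vehicle. The rule should be changed on grounds of safety and blinding.

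A reader might infer bias in the primary result or a loss of power. The documents do not support either as a material effect. The primary response analysis uses the full trial set (SAP sections 8.2.2 and 8.2.2.2), volumes are read by a blinded assessor (protocol section 13.2), patients who stop are followed up and analysed if willing (15.2), and section 12 plans analyses with and without unblinded participants. A power calculation that counted stopped tumours as non-responders would contradict that follow-up. The effect on the intention-to-treat result is expected to be small.

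The sensitivity analysis is more exposed: 4 to 5 tumours per arm for each affected patient. SAP section 8.2.2.2 names only the per-protocol sensitivity analysis and does not repeat the comparison with and without unblinded participants. The conclusion rests on reading section 12 as governing code breaks made under 15.2.

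**What to change.** State one rule in sections 15.2 and 12:
- A modified Draize score of 4 or above permanently stops the ointment on the reacting side, whatever the allocation, with no code break for that decision.
- The investigator, still blind, decides and records whether the other side must also stop because the vehicle is shared.
- Scheduled volume measurements at weeks 4 and 12 continue on both sides.
- Delete the conditional-stop sentence in 15.2 and the continuation offer in section 12.
- Keep code breaks for emergencies (section 10.4) and for safety reporting where causality or expectedness needs the allocation (sections 17.1 and 17.4).

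The change is to protocol wording only, but it has two costs. Some patients who react to vehicle lose treatment they might have chosen to continue. A one-side stop can also unbalance the per-protocol set: one active-side stop leaves 70 or 71 active tumours against 75 placebo, and a placebo-side stop does the reverse. Stopping both jars would take the same number from each arm. The imbalance touches only the sensitivity analysis, because the intention-to-treat analysis keeps those tumours. Reporting the number of one-side stops by arm alongside the per-protocol result would make it visible.
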